### Statistical analysis

Analyses will follow the intention-to-treat (ITT) principle, with participants analyzed in their randomized groups. The primary outcome, onset of a clinical ED by 2-year follow-up, will be analyzed using logistic regression with study condition as the independent variable. Results will be reported as odds ratios (ORs) with 95% confidence intervals (CIs). Secondary outcomes, including continuous measures of ED symptoms, body dissatisfaction, psychiatric symptom load, and QoL across five timepoints (baseline, post-intervention, 6 months, 1 year, and 2 years), will be analyzed using linear mixed-effects models (LMMs). These models will include fixed effects for study condition, time, and their interaction, with random intercepts for participants and groups to account for within-subject correlation and clustering of participants within groups. Where appropriate, random slopes for time will be explored. Effect estimates will be reported with 95% CIs.

Baseline characteristics will be summarized using descriptive statistics. Between-group comparisons will use *t* tests or Mann–Whitney *U* tests for continuous variables (depending on distribution) and *χ*^2^ or Fisher’s exact tests for categorical variables. Effect modification will be examined by testing interactions between intervention assignment and baseline psychiatric diagnosis, as well as between intervention assignment and diagnostic complexity (single versus multiple psychiatric diagnoses), via interaction terms in the regression models. Missing data will be handled using multiple imputations. All statistical tests will be two-tailed with *α* = 0.05.

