4	• Present and discuss homework from session 3 • Discuss how the ways in which we talk about our bodies may promote the thin ideal • Have participants come up with more positive alternative ways of talking about their bodies and encouraging participants to continue to challenge their body image issues in the future	As a **self-affirmation** exercise, choose three ideas to keep challenging your body image concerns and work toward developing a positive body image

Each group will consist of 6–8 group members as in previous studies [16, 23, 24]. The groups are led by two peers. The peers are trained young adults, preferably with personal experience of psychiatric illness, i.e., students within the area of health care (medicine, dietetics, psychology, and nursing).

All peers have received extensive and continuous training and supervision. The training will be made available as online sessions based on the manuscript and in collaboration with [name]. Fidelity assurance and continuous monitoring and evaluation of sessions will be performed during bimonthly supervision. Previous fidelity testing has shown high inter-rater agreement for the original Body Project [25].

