### Active control condition

The expressive writing (EW) serves as the active control condition and will consist of written instructions sent to participants weekly via text message over 4 weeks, asking them to write about their thoughts, emotions, images, and other content related to their body. They are encouraged to sit undisturbed for 40 min (no more, no less) and write only to themselves. If, after a while, they do not know what to write, they are encouraged to repeat what they have already written. This version of EW was used as earlier trials have found them equally credible to the Body Project [16].

The output is solely for the participants themselves and will not be read by others.

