### Power calculations

The incidence of new onset of ED over a period of 2 years is determined via the EDDI at baseline and 1- and 2-year follow-up. Based on the incidence of ED in the study by Ghaderi and colleagues, we expect significant differences between groups, with an incidence of ED in the control group of 8.8% and 2% in the intervention group [16]. We accept a significance level of 0.05 (*α*) and a power of 0.80 (*β*), leading to a sample size of 137 in each arm. To accommodate for potential attrition, we aim to include 150 in each arm. Attrition rates have been reported as increasing by 12% at 2 years and 19% at 4-year follow-up [21].

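### The primary logistic regression makes no allowance for clustering within Body Project groups, although the secondary models do; a time-constant group intercept may also leave the condition-by-time contrast uncorrected

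*Protocol article*

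**What the plan says.** All of this comes from the protocol article.

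- **Delivery, intervention arm** (The SMILE body project intervention): "Each group will consist of 6–8 group members", and two peers lead each group.
- **Delivery, control arm** (Active control condition): "written instructions sent to participants weekly via text message over 4 weeks". Each participant writes alone, for herself.
- **Primary outcome** (Statistical analysis): ED onset by 2 years "will be analyzed using logistic regression with study condition as the independent variable", reported as an odds ratio with a 95% confidence interval. No group term or robust variance is mentioned.
- **Secondary outcomes** (same paragraph): linear mixed models over five timepoints including baseline, with condition, time and their interaction, and "with random intercepts for participants and groups to account for within-subject correlation and clustering of participants within groups". Random slopes for time are to be explored where appropriate; the level at which they would apply is not stated.
- **Power calculations**: "with an incidence of ED in the control group of 8.8% and 2% in the intervention group", with no ICC or design effect.

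**The concern.** Women who share sessions, peers and discussion may have correlated outcomes. Controls share nothing comparable. The plan recognises this clustering for the secondary outcomes and then omits it from the outcome on which the trial will be judged. This goes beyond a detail lost in condensing, because both models are stated, side by side, and they treat the same feature of the design differently.

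A logistic model that takes 147 intervention participants as independent understates the variance of that arm's log odds whenever the ICC is positive. What is at stake is the coverage of the primary interval.

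The secondary models raise a narrower question. Randomisation follows the baseline assessment (Objectives of the SMILE trial), so groups cannot influence baseline values. A group intercept that is constant over time has the same value at baseline and at follow-up, and so drops out of a change-from-baseline contrast. Group variation that emerges after baseline is then missing from the standard error of the condition-by-time interaction.

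**Working it through.** **Inputs from the article.** Incidence 8.8% (control) and 2% (intervention); two-sided α = 0.05; 150 per arm; groups of 6 to 8. Taking m = 7, 150/7 ≈ 21 groups, so 21 × 7 = 147 per arm.

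**Assumed, because the article gives none.** ICC of 0.02, 0.05 and 0.10. For the mixed model: participant variance 0.6 and residual variance 0.4.

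**1. The plan's own sample size.** With the pooled formula and mean incidence 0.054,

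n = [z·√(2 × 0.054 × 0.946) + 0.8416·√(0.088 × 0.912 + 0.02 × 0.98)]² / 0.068².

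With z = 1.645 (one-sided) this is 135.6, so 136, close to the stated 137. With z = 1.960 (two-sided) it is 172.2, so 173. The stated 137 therefore contains no allowance for clustering. The one-sided/two-sided mismatch is a separate matter.

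**2. Design effect, intervention arm only.** DE = 1 + (m − 1) × ICC = 1 + 6 × ICC, which gives 1.12, 1.30 and 1.60.

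**3. Width of the primary interval at the planned rates.** Per participant, the variance of the log odds is 1/(0.02 × 0.98) = 51.02 in the intervention arm and 1/(0.088 × 0.912) = 12.46 in the control arm; the sum is 63.48. The ratio of true to model standard error is √[(DE × 51.02 + 12.46)/63.48]:

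- ICC 0.02: √(69.60/63.48) = 1.047
- ICC 0.05: √(78.79/63.48) = 1.114
- ICC 0.10: √(94.09/63.48) = 1.217

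**4. Type I error of the primary test.** With equal rates the large-sample ratio is √[(DE + 1)/2] = 1.030, 1.072 and 1.140. Putting 1.96/ratio into the normal tail gives 5.7%, 6.8% and 8.6%. The Wald test is conservative with few events, so simulation is the better guide (beta-binomial, 21 groups of 7 against 147 independent controls, common event rate 5.4% or 8.8%):

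| ICC | Large-sample approximation | Simulated Wald |
|---|---|---|
| 0 | 5.0% | 4.1-4.5% |
| 0.02 | 5.7% | 4.6-5.0% |
| 0.05 | 6.8% | 5.6-5.9% |
| 0.10 | 8.6% | 7.1-7.7% |

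Repeat runs differ by one or two tenths of a percentage point.

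**5. Condition-by-time contrast in the mixed model.** With a constant group intercept, the model variance of the difference in change is 4 × 0.4/147 = 0.01088, SE 0.104. If group effects arise only after baseline, the true variance adds ICC/21:

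| ICC | True SE | Model SE too small by | Implied type I error |
|---|---|---|---|
| 0.02 | √(0.01088 + 0.00095) = 0.109 | 4% | 6.0% |
| 0.05 | √(0.01088 + 0.00238) = 0.115 | 9% | 7.6% |
| 0.10 | √(0.01088 + 0.00476) = 0.125 | 17% | 10.2% |

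REML fits of the stated model gave mean interaction SEs of 0.104 (ICC 0.05) and 0.105 (ICC 0.10), which confirms that the group term contributes almost nothing to this contrast.

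**6. Between-arm difference at a single visit.** Here the group intercept does not cancel. Simulating 20 groups of 7 against 140 controls at ICC 0.02, 0.05 and 0.10, type I error is 4.8%, 4.8% and 5.5% if each control is her own group. It is 2.8%, 1.9% and 1.2% if all controls are coded as one group. These intervals are about right or too wide.

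**The case against.** Four points on the other side deserve weight.

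- **The primary effect is small at plausible ICCs.** This stands. At ICC 0.02 the conservatism of the Wald test roughly cancels the inflation. An ICC of 0.10 is strong for a rare event: at 5.4% incidence, the group-mate of a case would have a risk of 0.054 + 0.10 × 0.946 = 14.9%, nearly three times the average. A reader might infer that type I error exceeds 5% regardless; the calculations do not support that.
- **The mixed models already contain a group term.** This stands too. A reader might infer that the term is applied to both arms, or that controls are pooled into one group. The article says neither, and the coding of ungrouped controls is a detail that an article may leave to the full plan.
- **Random slopes may be explored.** A slope at group level would let group variation enter the change contrast. The article commits to none, so the cancellation holds for the model as stated but is conditional on no such slope being added.
- **The hypotheses concern all follow-up assessments.** Between-arm differences at each visit can be taken from the same model and are not materially affected. It would therefore be wrong to say that all secondary intervals are too narrow.

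None of this explains why the primary model omits a feature of the design that the next model in the same paragraph includes.

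**Conclusion.** The concern holds in a limited form. The primary analysis as written ignores clustering that exists in the intervention arm only, so its interval is too narrow for any positive ICC. At the planned rates the true standard error exceeds the model's by about 5%, 11% and 22% at ICC 0.02, 0.05 and 0.10. The effect on type I error is modest at 0.05 or below and clear only at 0.10. In the secondary models the shortfall is confined to condition-by-time contrasts, and requires that group effects arise after baseline and that no group-level slope is fitted. Its size also depends on the residual variance share, taken here as 0.4. All sizes rest on assumed ICCs and on about 21 groups of 7. The change should be made, but clustering of this size does not by itself undermine the trial.

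**What to change.** **Primary outcome.** Keep the logistic model and odds ratio, and state that standard errors will be cluster-robust with a small-sample correction, each Body Project group being a cluster and each control a singleton. Do not rely on a random-effects logistic model: 2% of 150 is about 3 expected intervention-arm events, spread over some 21 groups, so a group variance could hardly be estimated.

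**Secondary outcomes.** State that the group random effect applies to the intervention arm and to post-baseline visits only.

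**Cost.** A few sentences of analysis text and slightly wider intervals. Group membership is known from delivery, so no new data, visits or participants are needed.

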## Objectives of the SMILE trial

The present study aims to test the efficacy of the Body Project as a virtually delivered peer-led intervention for women with psychiatric illness and body dissatisfaction.

The primary aim of this study is to reduce the incidence of ED, measured by a clinical diagnostic interview after 2-year follow-up.

Secondary objectives are to examine whether the Body Project intervention leads to (1) reductions in eating disorder symptoms, body dissatisfaction, and thin-ideal internalization, and (2) improvements in QoL, loneliness, and overall psychiatric symptom burden across follow-up assessments.

The Body Project manual has been adapted to include elements relevant for individuals with psychiatric illness, with an increased emphasis on SoMe-related content.

After baseline assessment, participants are randomized to either:

(1) Body Project intervention, or (2) Active expressive writing control condition.

We propose the following hypothesis:I.The Body Project intervention will be effective in reducing incidence of ED (primary outcome) over a 2-year period compared to controls.II.The Body Project intervention will significantly reduce ED symptoms, body dissatisfaction, and thin idealization at all follow-up assessments.III.The Body Project will be effective in reducing total psychiatric symptom load, loneliness and QoL at all follow-ups compared to active controls.IV.Baseline psychiatric symptoms, SoMe use, and body dissatisfaction predict future increases in ED symptoms over a 2-year period.

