### Participants

We aim to recruit 300, 15–30-year-old, women with a psychiatric diagnosis, randomized 1:1 to the Body Project intervention or an active control condition. Participants are allocated using block randomization with varying block sizes and random permutations within each block to ensure allocation concealment and balance across study arms. All participants receive usual care for their psychiatric condition. A participant flowchart is illustrated in Fig. 1.

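### The secondary mixed models leave the arm difference at baseline free although randomisation makes it zero; this is valid but costs precision on every secondary contrast

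*Protocol article*

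**What the plan says.** All references are to the protocol article.

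- **Response.** Under Statistical analysis, the continuous secondary outcomes are measured "across five timepoints (baseline, post-intervention, 6 months, 1 year, and 2 years", and all five occasions enter linear mixed models. Baseline is therefore an outcome occasion, not a covariate.
- **Fixed effects.** "These models will include fixed effects for study condition, time, and their interaction". Neither a common baseline mean nor adjustment for the baseline score is mentioned.
- **Random effects.** The models are fitted "with random intercepts for participants and groups to account for within-subject correlation and clustering of participants within groups". Random slopes for time are only to be explored.
- **Order of events.** Under Objectives: "After baseline assessment, participants are randomized to either" the Body Project or the writing control. Under Participants, they are "randomized 1:1 to the Body Project intervention or an active control condition".
- **Use of the models.** Hypothesis II is that the intervention "will significantly reduce ED symptoms, body dissatisfaction, and thin idealization at all follow-up assessments". Hypothesis III makes a claim against active controls at all follow-ups.

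**The concern.** With baseline in the response and time categorical, the condition main effect is a freely estimated arm difference at baseline. Each condition-by-time term is then a difference between arms in raw change from baseline. Because allocation follows the baseline assessment, the design fixes the true baseline difference at zero. The model spends information on estimating a known quantity, and the sampling error of that estimate enters every follow-up contrast.

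Subtracting the whole observed baseline difference over-corrects for chance imbalance whenever the correlation between baseline and follow-up is below 1. The result is not bias but wider confidence intervals than the same data allow. It matters because hypotheses II and III claim effects at every follow-up on many scales, while the sample size was set for the binary primary outcome only, so the secondary outcomes have no stated power margin.

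**Working it through.** The article gives no power, standard deviation or correlation for the secondary outcomes, so there is no figure of its own to reproduce.

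**Inputs from the article.** Five occasions; 1:1 allocation; 150 per arm (Power calculations: "To accommodate for potential attrition, we aim to include 150 in each arm"); participant and group random intercepts; intervention groups of 6 to 8, taken here as 7.

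**Assumptions.** Outcome SD 1; categorical time; complete data; baseline-to-follow-up correlation ρ from 0.4 to 0.8; group intraclass correlation (ICC) 0.05 where a group effect is included. A random participant intercept implies the same ρ between all visits.

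**Step 1: variances, in units of 2·SD²/n.** Let d_t be the observed arm difference at follow-up t, and d_0 that at baseline.

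- Stated model, condition-by-time contrast: d_t − d_0, variance 2(1 − ρ).
- Stated model, plain arm difference at follow-up (main effect plus interaction): d_t, variance 1.
- Common baseline mean: d_t − ρ·d_0, variance 1 − ρ².

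The ratio of the third to the first is (1 − ρ²) / [2(1 − ρ)] = (1 + ρ)/2.

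**Step 2: one case in full, ρ = 0.5.** The unit is 2/150 = 0.01333. Stated model: 0.01333 × 1.00 = 0.01333, SE 0.115. Common baseline mean: 0.01333 × 0.75 = 0.01000, SE 0.100. The ratio is 0.75, a 25% cut in variance.

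**Step 3: the range, with and without the group intercept.** A time-constant group intercept cancels from the change contrast but not from the constrained estimate, so including it shrinks the gain. The last column comes from generalised least squares with groups of 7 in the intervention arm only.

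| ρ (assumed) | SE, stated | SE, common baseline | Variance ratio | Variance cut | Cut with group ICC 0.05 |
|---|---|---|---|---|---|
| 0.4 | 0.126 | 0.106 | 0.70 | 30% | 26% |
| 0.5 | 0.115 | 0.100 | 0.75 | 25% | 22% |
| 0.6 | 0.103 | 0.092 | 0.80 | 20% | 17% |
| 0.7 | 0.089 | 0.082 | 0.85 | 15% | 13% |
| 0.8 | 0.073 | 0.069 | 0.90 | 10% | 9% |

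**Step 4: other conditions.**

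- With 12% missing at 2 years (the attrition figure under Power calculations) and no group effect, the ratio is 0.77 at ρ 0.5 and 0.86 at ρ 0.7.
- If time is linear in calendar time, the cut in the variance of the slope contrast at ρ 0.5 is about 14% without the group effect and 11% with it.
- If the effect is read as the plain follow-up difference, the ratio is 1 − ρ²: 0.84, 0.75, 0.64, 0.51 and 0.36 for ρ 0.4 to 0.8. That reading does not recover the loss.

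**Step 5: what the remedy needs.** Under a random-intercept covariance, the common-baseline model subtracts b·d_0 at every visit, where b is the single working correlation. If the true correlation at a visit is r, the variance is 1 − 2br + b², against 2(1 − r) for the change contrast. The constrained estimate is no better once r ≥ (1 + b)/2, for example r ≥ 0.75 when b = 0.5. Baseline-by-time adjustment gives each visit its own slope and avoids this, as does an unstructured covariance.

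**The case against.** The strongest reply is that condition, time and their interaction with baseline in the response is a common and valid analysis. It is unbiased under randomisation, contradicts nothing in the article, and concerns secondary outcomes for which no power is claimed. All of that stands. A reader might infer that the secondary results would be biased by chance imbalance, that the trial is underpowered as a consequence, or that the primary result is at risk. The article supports none of these: there is no bias on average over randomisations, no stated figure fails, and the primary logistic regression does not use this model.

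A second reply is that the size is unknown. This also stands. The article gives no correlation or ICC, does not say whether time is categorical, does not name the treatment contrast, and leaves random slopes to be explored. Each could change the figures. A 15% to 25% cut in variance is also only about 8% to 13% off the standard error.

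A third reply is that an article leaves model detail to an analysis plan that is not shown. That covers time coding and contrasts, but not the main point: the fixed effects are stated, and a common baseline mean would change them.

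**Conclusion.** The point holds as one of efficiency. The stated secondary models estimate a baseline arm difference that the design sets to zero, and pay for it in precision for any correlation strictly between 0 and 1. With categorical time and a participant intercept, the avoidable part of the variance of each condition-by-time contrast is 30% to 10% for assumed correlations of 0.4 to 0.8, or about 26% to 9% with the planned group intercept at an assumed ICC of 0.05. It is smaller again if time is linear in calendar time, and it shrinks as the correlation approaches 1. For scale only: with an assumed effect of 0.3 SD at 2 years, ρ 0.5, complete data and no group effect, power is 0.74 as written and 0.85 with a common baseline mean.

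**What to change.** Revise the description of the secondary models before outcomes are compared by arm. Treat time as categorical, and name one of these:

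- **(a)** Model the four follow-ups with the baseline score as covariate, including baseline by time, and keep the participant and group random effects.
- **(b)** Fit a constrained longitudinal model to all five occasions, with a common baseline mean, condition-by-time terms at the four follow-ups only, and an unstructured within-participant covariance; keep the group effect.

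The two agree closely only under such a covariance, so they should not be offered as interchangeable. Report the arm difference at each follow-up, with its 95% confidence interval, from the chosen model.

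The cost is a sentence or two in the analysis section. No new data are needed, because the baseline scores are already collected.

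### The default secondary mixed model assumes one constant within-person correlation over visits 1 to 24 months apart; if correlation decays, change-from-baseline standard errors are too wide post-intervention and too narrow at 2 years

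*Protocol article*

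**What the plan says.** The Statistical analysis section applies linear mixed models to the continuous secondary outcomes "across five timepoints (baseline, post-intervention, 6 months, 1 year, and 2 years". On the fixed part it says: "These models will include fixed effects for study condition, time, and their interaction". The random part is given as "with random intercepts for participants and groups to account for within-subject correlation and clustering of participants within groups", so the participant intercept is the named device for correlation within a woman. The only relaxation offered is this: "Where appropriate, random slopes for time will be explored". No other residual covariance and no robust standard error is mentioned. The section does not say whether time is categorical or continuous, or which arm contrast is reported.

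Under Objectives, hypothesis II says that the intervention "will significantly reduce ED symptoms, body dissatisfaction, and thin idealization at all follow-up assessments". Hypothesis III is likewise framed at every follow-up against the active control.

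**The concern.** A participant intercept with independent residuals is compound symmetry: one variance for all visits and one correlation for all pairs. The group intercept is also constant over visits, so it does not relax this. The visits are far from equally spaced. The control exercises are sent "weekly via text message over 4 weeks", which puts the post-intervention visit about 1 month after baseline (an inference, since the visit date is not stated), and the last visit is at 24 months.

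With visit as a category, each interaction term is the arm difference in change from baseline, and its variance depends on the correlation of that visit with baseline. The default model gives all four follow-ups the same value. If the true correlation declines with the gap, the immediate effect is tested with too little power and the 2-year effect with too lenient an error rate. Hypotheses II and III rest on these models.

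**Working it through.** **Inputs from the Protocol article.** Five visits, placed at 0, 1, 6, 12 and 24 months (the 1 is inferred); "we aim to include 150 in each arm"; women "randomized 1:1 to the Body Project intervention or an active control condition"; two-sided 5% tests. The article gives no SD, correlation or standard error for any secondary scale, so there is no planned figure to reproduce.

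**Assumptions.** SD 1 at every visit, categorical time, complete data, group clustering left out. Main scenario: corr(gap) = 0.40 + 0.35 × exp(−gap/8 months). Correlations with baseline are then 0.71, 0.57, 0.48 and 0.42 at the four follow-ups.

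**Formulas.** For a correlation ρ between baseline and the visit, the standard error of the difference in change is √(4(1 − ρ)/n), with n = 150 per arm. The large-sample random-intercept fit replaces every ρ by the mean of the ten pairwise correlations, here 0.515. With r = model SE / true SE:

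- r = √((1 − 0.515)/(1 − ρ))
- type I error = 2Φ(−1.96 r)
- power where the true power is 80% = Φ(2.80 − 1.96 r)

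**Main scenario, intercept only.** Post-intervention, the true SE is √(4 × 0.291/150) = 0.088 and the model SE is √(4 × 0.485/150) = 0.114, so r = 1.29. Power is Φ(2.80 − 2.53), about 61%.

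| Visit | ρ with baseline | r | Type I error |
|---|---|---|---|
| Post | 0.71 | 1.29 | 1.1% |
| 6 months | 0.57 | 1.06 | 3.8% |
| 1 year | 0.48 | 0.96 | 5.9% |
| 2 years | 0.42 | 0.91 | 7.4% |

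A simulation of 2,000 null data sets with REML fits and dropout of 3/6/9/12% gave type I errors of 1.2%, 3.7%, 5.8% and 7.7%. A further 1,000 data sets with an effect gave 62% power at post.

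**Main scenario, random linear slope added.** At 2 years r = 1.04 (type I error 4.2%). Post-intervention r = 1.19, so 80% power becomes Φ(2.80 − 2.34), about 68%.

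**Sensitivity to the assumed decay.**

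| Correlation, 1 to 24 months | Post r, intercept | Post r, slope | 2-year r, intercept (type I) | 2-year r, slope |
|---|---|---|---|---|
| Exponential 0.80 to 0.40 | 1.43 | 1.21 | 0.825 (10.6%) | 1.03 |
| Power 0.80 to 0.40 | 1.57 | 1.42 | 0.91 (7.6%) | 1.05 |
| Exponential 0.70 to 0.50 | 1.15 | 1.06 | 0.89 (8.0%) | 1.02 |
| Power 0.70 to 0.50 | 1.21 | 1.15 | 0.94 (6.6%) | 1.03 |
| Exponential 0.60 to 0.55 | 1.03 | 1.01 | 0.97 (5.7%) | 1.00 |
| Power 0.60 to 0.55 | 1.04 | 1.03 | 0.98 (5.4%) | 1.01 |
| Flat 0.60 | 1.00 | 1.00 | 1.00 (5.0%) | 1.00 |

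**The other possible contrast.** For the plain arm difference at one visit the SE is √(2/n) × SD, which does not contain ρ. In the main scenario r is 1.000 at all four follow-ups with complete data, and between 0.991 and 1.004 with the dropout above. This relies on equal variances.

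**Unequal variances.** If the SD also grew from 0.8 to 1.2 over follow-up in the main scenario, 2-year type I error for the change contrast under the intercept-only model would be 7.8% (equal steps per visit) to 9.4% (linear in time). That growth is an assumption too.

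**The case against.** A reader might infer that the plan forces wrong standard errors on every visit comparison and that the 2-year secondary results will be anti-conservative. The article does not support that, for four reasons.

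- **The slope is allowed.** The sentence after the random intercepts permits random slopes, and a linear slope removes the 2-year understatement in every scenario checked.
- **The decay is not documented.** No correlation is given for any scale. With a flat correlation the model is exact, and with a nearly flat one the error is negligible.
- **The contrast is not fixed.** Effects at all follow-ups could equally mean arm differences at each visit, which are unaffected under equal variances. If time were linear, four separate visit contrasts would not exist.
- **The model is a standard one.** An article may leave covariance detail to an analysis plan.

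The first three limit the size of the point and make it conditional. They do not remove it. The interaction terms that the article does name are change contrasts when visit is categorical, and hypotheses worded for every follow-up point towards categorical visits. The slope has no rule for its use, so the covariance would be chosen after seeing the data. It also repairs the problem only in part: wherever correlation clearly decays, the post-intervention standard error stays too wide. On the fourth, the random intercept is a stated method and not an omitted detail. The suggested structure is valid whether or not correlation decays; the default is valid only if it does not.

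**Conclusion.** The point holds as a conditional weakness in a stated method. If within-person correlation falls with the gap, the intercept-only model misstates the change-from-baseline standard errors in opposite directions at the two ends of follow-up. In the main assumed scenario the post-intervention standard error is about 29% too wide and the 2-year one about 9% too narrow (type I error 7.4%). The error ranges from nil with constant correlation to a 2-year type I error of 10.6% under the steepest exponential decay tabulated.

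These sizes rest on assumed correlations, equal variances, categorical time, contrasts against baseline and an inferred 1-month visit. The primary outcome is analysed by logistic regression and is untouched.

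**What to change.** For the continuous secondary scales, state the following in the analysis plan:

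- visit as a categorical factor, with an unstructured within-participant covariance over the five visits and Kenward-Roger degrees of freedom, in place of the participant random intercept and the exploratory slopes;
- the term for clustering within intervention groups kept;
- a fallback fixed in advance for non-convergence, for example heterogeneous Toeplitz and then robust standard errors;
- the arm contrast to be reported at each visit, named as change from baseline or as difference at the visit.

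The cost is a few lines of text. The within-participant part goes from 2 covariance parameters (intercept and residual variance) to 15 (five variances and ten covariances), which is modest for 300 women. Some scales may not converge, which is why the fallback has to be set beforehand.
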